### Outcome and objectives

The primary outcome of this pilot study with the monti platform will be the accuracy of detecting episodes with diagnosed ADHF by a self-supervised contrastive learning-derived risk index based on wearable-recorded time series assessed through *C*-statistics (*Table 4*). As a secondary outcome data integrity will be assessed through the percentage of wearable data per day, the time difference between logged time point of measurement and database, and the score in the SUS, will be evaluated. Additionally, several exploratory endpoints will be examined.

**Table 4 ztaf004-T4:** Objectives and outcome measures of the CONAN study

	Outcome measures
Primary objective	
Assess the capability of the self-supervised contrastive learning-derived risk index (from wearable-recorded time series) to detect episodes of acute decompensated heart failure (ADHF).	Area under the receiver operating characteristics (AUROC) curve for detecting episodes of diagnosed ADHF.
Secondary objective	
(2) Evaluate the data integrity of the *monti*-monitoring platform in terms of adherence, technical functionality, and data quality.	Adherence: Daily percentage of wearable data availability. Percentage of data availability over participation period. Availability of each parameter per day. Number of app-server connection attempts. Number of uploaded vital signs. Number of recorded ECGs. Number of dropouts. Technical functionality: Ratio of failed uploads to total uploads. Number/type of notifications sent via the app. Number/type of user contacts. Mean time difference between measurement and database logging. Data quality: Mean percentage of data with high quality indices determined by the wearable for each parameter per day.
(3) To assess usability of the mobile *monti* platform	Mean score on the System Usability Scale (SUS). Percentage of users rating the app as ‘easy to use.’
(4) Monitor adverse events, including device-related effects and deficiencies.	Number of skin reactions or discomfort. Number of observed device damages.
Explorative objective	
(5) Expansion of the dataset by including additional ‘regular’ episodes	Number of ‘regular’ episodes included for training, annotated based on the 2-day window of study visits. Number of the additional ‘regular’ episodes included for training, annotated based on patient-reported stable symptoms and vital signs via the app. AUROC detecting episodes with diagnosed ADHF with expanded training data.
(6) Assess detection capabilities using pre-trained neural networks.	Number of ‘regular’ episodes used for training. AUROC detecting episodes with diagnosed ADHF using pre-trained neural networks.
(7) Conduct subgroup analyses based on patient characteristics: sex, age, digital health literacy, quality of life (KCCQ-12), self-care behaviour (EHFScB-9), and inpatient vs. outpatient settings.	Area under the receiver operating characteristics (AUROC) curve for detecting episodes of diagnosed ADHF. Dropout rate. Percentage of wearable data availability over participation. Daily app-server connection attempts.
(8) Assess the robustness of clinical congestion assessments.	Correlation of congestion ratings based on clinical assessment with EVEREST Score. Correlation of clinical assessments with app-integrated symptom inventory.
(9) Evaluate the usability of the mobile *monti* platform using alternative scales.	Mean score on the Mobile Application Rating Scale (MARS-G). Correlation between SUS and MARS-G scores.
(10) Compare bioelectrical impedance analysis to clinical congestion assessments.	Correlation of clinical congestion assessment with total and extracellular body water (via bioelectrical impedance). Correlation of bioelectrical impedance analysis with wearable-measured bioelectrical impedance.
(11) Assess the *monti* platform impact on patient self-management, and quality of life.	Change in EHFScB-9 score (baseline to Day 90). Change in KCCQ-12 score (baseline to Day 90).

### Statistical analysis

The sample size calculation was based on a 20% incidence rate of congestion, an 85% detection sensitivity of the risk index (see below), a 15% dropout rate, a 10% error tolerance, and a significance level of 0.05, indicating a need for ∼282 patients to achieve sufficient statistical power.

For statistical analysis differences between means of hours annotated as ‘regular’ and ‘congested’ obtained from risk score will be tested for significance using a two-sided *t*-test test, adjustment for multiple comparisons is performed by using Bonferroni correction. To address overfitting, a 10-fold cross-validation will be performed. Statistical significance will be tested by an analysis of variance within the cross-validation splits of ADHF and regular. Receiver operating characteristics analysis [area under the curve of the ROC-analysis (AUROC)] will be computed to assess the primary endpoint. The cut-point that optimizes the detection of true positive results (sensitivity) and false positive results (1-specificity) is reported by the Youden index. For clinical requirements (not missing an event), specificity will additionally be reported at a sensitivity of ∼95%.

To assess risk score prediction capabilities for congestion detection, the performance of the score up to 7 days before and after the timestamp of diagnosis (t = 0 h) will be analysed. For AUROC-analysis, 95% confidence intervals are reported. A *P*-value of <0.05 will be considered significant. For data and statistical analysis, an open-source software tool will be used.

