**Methods and results:**

This is the protocol for a single-arm, prospective cohort pilot study that will include 290 patients with ADHF. Acute decompensated heart failure is diagnosed by clinical signs and symptoms, as well as additional diagnostics (e.g. NT-proBNP). Patients will receive standard-of-care treatment, supplemented by continuous wearable-based monitoring of vital signs and physical activity, and are followed for 90 days. During follow-up, study visits will be conducted and presentations without clinical ADHF will be referred to as ‘regular’ and data from these episodes will be presented to a deep neural network that is trained by a self-supervised contrastive learning objective to extract features from the time-series that are typical in regular periods. The model is used to calculate a risk index measuring the dissimilarity of observed features from those of regular periods. The primary outcome of this study will be the risk index’s accuracy in detecting episodes with ADHF. As secondary outcome data integrity and the score in the validated questionnaire System Usability Scale will be evaluated.

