## Introduction

Heart failure (HF) is the most common cause of hospitalization and in-hospital death in Germany.^1^ After discharge, 17% of patients with HF are rehospitalized for HF within 90 days.^2^ Recurrent hospitalizations of respective patients due to HF increase the risk of adverse events, and these are associated with high mortality rates of almost 12%.^3,4^ Up to 70% of HF-related hospitalizations are driven by acute decompensated HF (ADHF).^5^ Acute decompensated HF can be triggered by various mechanisms such as hypertensive episodes or arrhythmias.^6,7^ Hitherto, outpatient management of HF patients relies on self-assessment of symptoms and tracking of single parameters like body weight. This approach places a significant burden on patients, requiring them to handle standardized parameters and possess a certain level of health literacy.^8^ To reduce the risk of hospitalizations, patients with HF are frequently re-examined and clinically assessed according to fixed schedules to detect decompensation early.^9^ These visits involve clinical assessment with specialized personnel, laboratory measurements, and adjunctive diagnostic modalities, which are resource-intensive and pose a significant burden to specialized outpatient clinics.^10^ Hence, there is a need for innovative and individualized concepts for pre-emptive detection of congestion in patients with HF that reduce the burden on the healthcare system.

Implementation of digital tools for assessing early clinical signs of congestion represents an option for the management of patients with HF and potentially facilitates early treatment interventions.^11^ Cardiac implantable electronic devices and implantable pulmonary artery pressure sensors are promising methods for detecting congestion early; however, they require an invasive implantation procedure.^11,12^ Devices measuring bioelectrical impedance show comparable results in detecting congestion; however, they require active patient engagement.^13^

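### The sample-size statement reports power, but 282 is a precision calculation for sensitivity rather than for the primary AUROC, and its dropout step falls short of the 289 needed

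*Protocol article*

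**What the plan says.** The Statistical analysis section of the protocol article opens with the inputs: "The sample size calculation was based on a 20% incidence rate of congestion, an 85% detection sensitivity of the risk index", together with "a 15% dropout rate", an error tolerance of 10% and a significance level of 0.05. It concludes by "indicating a need for ∼282 patients to achieve sufficient statistical power". It states no power value, no null or comparison value and no assumed AUROC. The 85% carries a pointer to later text, but the later text describes the ROC analysis and does not derive that figure.

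The primary outcome measure in Table 4 (Outcome and objectives) is "Area under the receiver operating characteristics (AUROC) curve for detecting episodes of diagnosed ADHF", and the Statistical analysis section confirms that the AUROC assesses the primary endpoint.

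The abstract describes a "prospective cohort pilot study that will include 290 patients with ADHF". Nothing in the article explains how 282 and 290 relate.

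**The concern.** Three things do not fit together.

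- A power claim needs a hypothesis, an effect and a power level, and the inputs include none of these. An expected sensitivity, an error tolerance and an incidence are what one supplies to fix the width of a confidence interval.
- The interval in question is for sensitivity, while the study is to be judged on the AUROC. A reader who sees a power statement in the same section as the primary analysis may take it that the primary endpoint was powered.
- 282 is what results from adding 15% to 245. Adding 15% does not leave 245 after 15% are lost.

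At stake are how the result may be described afterwards and whether the stated sample size delivers the stated tolerance. The feasibility of the study is not at stake.

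**Working it through.** **Inputs** (all from Statistical analysis, except the 290 from the abstract): incidence 0.20; sensitivity Se = 0.85; error tolerance d = 0.10; significance level 0.05, taken as two-sided, so z = 1.96; dropout 0.15; planned enrolment 290.

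**Reproducing 282.**
- Cases needed: z² × Se × (1 − Se) / d² = 3.8416 × 0.1275 / 0.01 = 48.98, so 49.
- Patients needed before dropout: 49 / 0.20 = 245.
- Multiplied by 1 + 0.15: 245 × 1.15 = 281.75, so 282. This matches.

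**Other readings of the same inputs do not give 282.**

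| Reading | Patients |
|---|---|
| One-sided z | 198 (× 1.15) or 203 (/ 0.85) |
| 10% as the full interval width, / 0.85 | 1,152 |
| One-sample test of 0.85 against 0.75, 80% or 90% power, one- or two-sided | 590 to 1,004 |

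The 0.75 in the last row is my assumption, since the article gives no null value. Of the readings tried, only the precision formula fits, and power does not enter it.

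**Correct allowance for dropout.** To keep 245 after losing 15%: 245 / (1 − 0.15) = 288.2, so 289. The difference from 282 is 7 patients.

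**What each enrolment delivers.** Retained = N × 0.85; cases = retained × 0.20; half-width = 1.96 × √(0.1275 / cases).

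| Enrolled | Retained | Cases | Half-width (points) |
|---|---|---|---|
| 282 | 239.7 | 47.9 | 10.1 |
| 290 | 246.5 | 49.3 | 9.97 |

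So 282 just misses the stated tolerance and 290 just meets it.

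**Precision for the AUROC.** The article gives no assumed AUROC, so a range is needed. The Hanley-McNeil variance is [A(1 − A) + (m − 1)(B₁ − A²) + (k − 1)(B₂ − A²)] / (mk), with B₁ = A / (2 − A), B₂ = 2A² / (1 + A), m cases and k non-cases. It assumes one independent observation per patient. With N = 290, m = 49.3 and k = 246.5 − 49.3 = 197.2:

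| Assumed AUROC | 95% half-width |
|---|---|
| 0.70 | 0.088 |
| 0.80 | 0.078 |
| 0.85 | 0.070 |
| 0.90 | 0.059 |

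At N = 282 the range is 0.089 to 0.060, practically the same.

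**The case against.** **Sizing a single-arm pilot on sensitivity is defensible.** Sensitivity is a coordinate of the ROC curve, the plan reports a Youden cut-point, and the sample-size sentence does not itself name the AUROC. This stands. The fault is not the choice of quantity; it is that the result is called power and its distance from the primary endpoint is not stated.

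**The dropout slip hardly matters.** This also stands. It is 7 patients, about 1 case and 0.1 point, on a figure marked as approximate, and the announced 290 already covers it.

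**A reader might infer that 282 and 290 contradict each other.** They need not. One is a calculated need and the other an enrolment plan, and enrolling 290 satisfies a need for 282. What can be said is that the article does not link them. That 290 is 289 rounded up is plausible but nowhere stated.

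**A reader might infer that the 20% incidence conflicts with the Introduction,** where "17% of patients with HF are rehospitalized for HF within 90 days". The two figures count different events. The 17% is readmission for heart failure. The study enrols outpatients as well as inpatients and assesses congestion at routine and unplanned visits (Study procedures, Table 2), so ADHF found without readmission counts, and a rate above 17% is not surprising. Multiplying the 17% by the Introduction's upper figure of 70% for ADHF-driven admissions would be weaker still: that figure is a ceiling for heart failure admissions in general, not a share of readmissions in patients enrolled with ADHF. Precision at 17% is at most an optional sensitivity figure: 290 × 0.85 × 0.17 = 41.9 cases and a half-width of 10.8 points (282: 11.0).

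**A single AUROC half-width would be an unsupported number.** Agreed. The 85% in the plan is a sensitivity, not an AUROC, and the data will be hours and visit windows clustered within patients (Data collection). Any such figure has to be a range with its assumptions attached.

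**Conclusion.** The point holds. The article claims statistical power that its inputs cannot yield. The number is a 95% precision calculation for sensitivity, not for the primary AUROC, and the dropout allowance was added where it should have been divided out, giving 282 instead of 289.

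The size is modest: 282 gives a half-width of 10.1 points and 290 gives 9.97, against a tolerance of 10. No enrolment beyond the announced 290 is needed.

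The conclusion rests on reading the significance level as two-sided and the 10% as an absolute half-width. That reading reproduces 282 exactly, and none of the alternatives tried does. It also takes one case per affected patient and incidence and dropout as the article assumes them.

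A reader might go further and conclude that the study is too small for its primary endpoint. The documents do not support that: they set no AUROC target or required precision against which 290 could be found wanting.

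**What to change.** In Statistical analysis:

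- Replace 282 by 289 (245 / 0.85), add that planned enrolment is 290, and use the same 290 in the abstract and the Methods.
- Replace the closing reference to power with wording such as: *for a 95% confidence interval half-width of 10 percentage points for sensitivity*.
- Add one sentence saying that the primary AUROC was not formally powered.
- If AUROC precision is reported, give it as an assumption-based range: about ±0.06 to ±0.09 for an AUROC of 0.90 down to 0.70, with one independent observation per patient.
- Optionally, add the precision for sensitivity at a 17% incidence (about ±11 points), labelled as a sensitivity figure.

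The cost is a few lines of text. Enrolment, procedures and analyses do not change.

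### The sample size assumes sensitivity at a fixed cut-off, but the Youden cut-point is taken from the study's own ROC curve with no separate evaluation data named; on the same cases, sensitivity would be about 4 points too high

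*Protocol article*

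**What the plan says.** All of this is in the Protocol article, Methods, Statistical analysis, unless another place is named.

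- Sizing: congestion is assumed in 20% of patients, together with "an 85% detection sensitivity of the risk index (see below), a 15% dropout rate, a 10% error tolerance". Alpha is set at 0.05, and the resulting number is about 282 patients. The abstract gives 290 patients.
- First operating point: "The cut-point that optimizes the detection of true positive results (sensitivity) and false positive results (1-specificity) is reported by the Youden index".
- Second operating point: "specificity will additionally be reported at a sensitivity of" about 95%, with the clinical reason that events should not be missed.
- Safeguards: a 10-fold cross-validation against overfitting (Statistical analysis) and a 90/10 train/test split (Data collection). The network is trained on regular hours only (Data collection).
- Intervals: 95% confidence intervals are promised for the AUROC analysis. None is mentioned for sensitivity or specificity.
- Primary outcome: the AUROC (Outcome and objectives, Table 4), which needs no threshold.

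No threshold is fixed in advance, and the text does not say on which data either threshold is chosen or evaluated.

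**The concern.** The precision formula behind the sample size treats sensitivity as a simple proportion at a cut-off that does not depend on the data. The analysis instead takes the cut-off that looks best on the study's ROC curve. When such a cut-off is judged on the cases that selected it, the apparent sensitivity is too high on average and the usual binomial interval is too narrow.

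Cross-validating the network does not remove this. Even if every risk score comes from a model that never saw that patient, picking the Youden point on the pooled scores and reading sensitivity off the same curve is still selection and evaluation on one sample.

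At stake is the quantity on which the study was sized. A sensitivity a few points too high, with an interval that covers too rarely, would describe the risk index better than it performs.

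**Working it through.** **1. The plan's own figure.** Inputs from the Statistical analysis section: sensitivity 0.85, tolerance 0.10 (read as the half-width of a 95% interval), incidence 0.20, dropout 15%, z = 1.96.

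- Cases: 1.96² × 0.85 × 0.15 / 0.10² = 48.98, so 49.
- Patients: 49 / 0.20 = 245.
- Dropout: 245 × 1.15 = 281.75, so 282, as stated. (Dividing instead, 245 / 0.85 gives 289, close to the 290 in the abstract.)

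Expected evaluable cases are 282 × 0.85 × 0.20 = 47.9 (half-width 10.1 points) or 290 × 0.85 × 0.20 = 49.3 (half-width 9.97 points). The sizing is therefore for one sensitivity, at a fixed cut-off, in about 49 cases.

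**2. Effect of choosing the cut-point on the same cases.** Assumptions, not in the document: binormal scores, one independent score per patient, 49 ADHF and 245 − 49 = 196 regular. The best cut-point is set to 85% sensitivity and 85% specificity (AUROC 0.93) to match the design; 20,000 simulated studies.

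| | Cut-off fixed in advance | Youden, same cases |
|---|---|---|
| Mean apparent sensitivity | 85% (unbiased) | 87.8% |
| Mean true sensitivity at the cut-off used | 85% | 83.9% |
| Bias in sensitivity | 0 | 87.8 − 83.9 = 3.9 points |
| Bias in specificity | 0 | 0.9 points |
| 95% bound on the error in sensitivity | 9.5 points | 11.6 points |
| Coverage of the nominal 95% Wald interval | 94% | about 80% |

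Over five scenarios with AUROC from 0.76 to 0.94, the sensitivity bias is 3.4 to 5.4 points, the specificity bias 0.8 to 1.3 points, the error bound 11.5 to 15.1 points and the coverage 78% to 84%. Where the true sensitivity is near 85%, the bias is 3.4 to 4.2 points and the bound 11.5 to 12.3 points.

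**3. Dependence on the number of cases.** With 240 cases (for example if index episodes count) and an assumed 600 regular episodes, the same model gives a sensitivity bias of about 1.4 points.

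**4. The point at about 95% sensitivity.** With 49 cases the threshold is set by the two or three lowest-scoring ones: 46/49 = 93.9%, 47/49 = 95.9%. At AUROC 0.93 the mean apparent specificity is 66.8%, the true specificity at the chosen threshold 66.8%, and the true ROC value 66.6%, so there is no material bias. The central 95% range of the apparent specificity is 42% to 85%. The true sensitivity at the chosen threshold averages 94.0%, with a range of 86% to 99%.

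**The case against.** The strongest reply is that selection and evaluation on the same data is nowhere written. The article says cross-validation is done against overfitting without limiting its scope, and mentions cross-validation splits of both ADHF and regular data, so the splits may also serve evaluation. It is a condensed article, and nesting of thresholds is often left to an analysis plan. This stands in part: same-sample use is the natural reading, not a stated fact, and the size given here is conditional on it. It does not dispose of the point, because the sizing assumption (fixed cut-off) and the stated rule (cut-point optimised on the study's ROC) stand in the same section and do not match.

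Three stronger readings are tempting and are not supported:

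- A reader might infer that all reported sensitivities and specificities are optimistic. Only the Youden sensitivity is materially so. Youden specificity moves by about 1 point, and the specificity at about 95% sensitivity is imprecise rather than biased.
- A reader might infer that the primary result is compromised. The AUROC does not depend on any cut-point, and sensitivity and specificity are not listed as outcome measures in Table 4.
- A reader might infer that the cut-point will be carried into the later randomised study. The Limitations section names such a study as the next step but says nothing about the cut-point.

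The count of 49 is also implied rather than stated. Data are split into hours, the unit of the ROC analysis is not fixed, and every participant enters with ADHF. Labels are tied to follow-up visits, which favours the smaller count, but a larger count would shrink the bias.

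**Conclusion.** The point holds in conditional form. The study is sized for sensitivity at a fixed cut-off, while the plan selects the Youden cut-point from its own ROC analysis and names no separate data for judging it. If the same cases serve both purposes, and each of about 49 cases contributes one independent score, the planned precision is missed by about 2 points (about 12 instead of 10), sensitivity is overstated by about 4 points, and the usual interval covers about 80%. With about 240 cases the bias would be about 1.4 points. The shortfall is moderate and comes from selecting on the evaluation sample, since 49 cases with a fixed cut-off do deliver the planned precision. At the second operating point the weakness is imprecision without a promised interval.

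**What to change.** - State that the Youden threshold is chosen within the training patients of each fold, with folds split by patient, and that sensitivity and specificity are reported in the held-out patients, pooled over folds. A bootstrap optimism correction is an acceptable alternative.
- Give 95% confidence intervals for both operating points from a bootstrap that resamples patients and repeats the threshold choice in each resample.
- State the unit of the ROC analysis and whether index episodes count as cases, since the size of the bias depends on it.

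A single split of the cases into a selection half and an evaluation half is less attractive: with about 24.5 cases the half-width is 1.96 × √(0.85 × 0.15 / 24.5) = 0.14, or about 14 points.

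The cost is code and wording, best settled before results are seen. No extra patients are needed and the primary endpoint is unchanged. The reported Youden sensitivity will fall by a few points.

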### Data collection

Wearable data and ePRO data will be transmitted by monti via mobile data services to a centralized server that runs real-time data analysis and analysis software. The data recorded by the wearable will include time-series data of raw signals as well as vital signs and physical activity parameters, with the latter computed using proprietary algorithms provided by the manufacturer. Vital signs and physical activity parameters, such as heart rate, temperature, respiratory rate, and physical activity, will be recorded at a rate of up to 1 Hz. Thus, up to 3600 data points are potentially generated per hour, each paired by a corresponding quality index. On the platform backend, data integrity is assessed by monitoring actual wearing time, both initial and ongoing app usage, and overall data quality. Data integrity assessments are conducted at interim study visits and the study’s conclusion (*Table 2*).

Clinical records (visit entries, laboratory results, diagnostic results) will be documented in worksheets. Records will be independently and retrospectively reviewed by two cardiologists for the presence of ADHF. Worksheet entries and results of the validated questionnaires are transferred into a database.

Time-series data recorded by the wearable will be annotated based on clinical records. At each follow-up visit, where a clinical congestion assessment is conducted, the 2 days prior and post-visit are annotated as either ADHF or regular, as determined by the congestion assessment on the visit day.

Exploratively, the dataset of regular episodes may be enriched by including episodes beyond this initial 2-day window if patients report stable symptoms and vital signs through the app. This approach allows for the evaluation of whether these additional episodes show consistent ‘regular’ patterns suitable for model training. Datasets will be split into hours according to their timestamps, and only hours with a >90% amount of data points will be included to ensure sufficient information content among hours. No predefined quality constraints are used.

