To calculate the risk index, ‘regular’ hours collected during the study are used to train a deep neural network with a self-supervised contrastive learning objective, extracting features typical of regular periods. Training and test data are split 90/10. The model is used to calculate a risk index that measures the dissimilarity to regular features. The detection and predictive performance of the risk index will be compared to clinical documentation of ADHF. To evaluate the risk index’s predictive capabilities over time, the timestamp of the clinical ADHF diagnosis will be used as a reference point. The risk index computed by the model will subsequently be examined for the days preceding an ADHF event. This analysis aims to identify early deviations in the risk index that could potentially be driven by subclinical changes in physical activity or vital sign patterns.

Data collection will be conducted following an intention-to-treat approach and will continue until withdrawal, except in cases where there is a specific request to delete all individually recorded data.

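### The specificity at about 95% sensitivity is meant to protect against missed events, but the stated risk-score analysis is hourly and nothing turns the hours of a visit window into one episode result

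*Protocol article*

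**What the plan says.** Two statements are made per event. Table 4 (Outcome and objectives) gives the primary measure as "Area under the receiver operating characteristics (AUROC) curve for detecting episodes of diagnosed ADHF". The Statistical analysis section adds: "For clinical requirements (not missing an event), specificity will additionally be reported at a sensitivity of" about 95%.

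The processing is described per hour:
- Data collection, segmentation and filter: "Datasets will be split into hours according to their timestamps, and only hours with a >90% amount of data points will be included".
- Data collection, training: the hours labelled regular train the network.
- Statistical analysis, comparison: "differences between means of hours annotated as ‘regular’ and ‘congested’ obtained from risk score will be tested for significance".

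The label itself arises once per visit and is spread over time: "the 2 days prior and post-visit are annotated as either ADHF or regular, as determined by the congestion assessment on the visit day".

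The Statistical analysis section then lists the ROC analysis, the Youden cut-point and the 95% point. It does not say whether the units counted are hours or episodes, and it gives no rule for combining hours.

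**The concern.** Sensitivity means different things on the two scales. Per hour, it is the share of ADHF-labelled hours above the cut-off. Per event, it is the share of decompensations detected. Only the second matches the stated purpose of not missing an event.

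A visit window can contribute up to about 96 hours that all inherit one clinical judgement. A cut-off leaving 5% of those hours below it says nothing definite about how many episodes are missed, because that depends on how the missed hours are distributed over episodes. A reader will nevertheless take the reported specificity as the price of missing about one decompensation in twenty. The same open unit affects the primary AUROC and the Youden cut-point. If the unit and the summary are chosen after the results are seen, the more favourable version can be reported.

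**Working it through.** **1. The plan's own figure counts events.** Inputs from Statistical analysis: sensitivity 85%, error tolerance 10%, incidence 20%, dropout 15%, significance level 0.05 (taken as two-sided).
- Events: 1.96² × 0.85 × 0.15 / 0.10² = 48.98, about 49.
- Patients: 48.98 / 0.20 = 244.9.
- With dropout: 244.9 × 1.15 = 281.6, i.e. the stated 282.
- Expected events: 282 × 0.85 × 0.20 = 47.9, about 48.

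So the detection sensitivity behind the sample size is a proportion of about 49 events. An hourly ROC would use the word for another quantity in the same section.

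**2. Hours per label.** Two days before plus two days after a visit: 4 × 24 = 96 hours. This is a ceiling, because the filter requires more than 90% of data points per hour and the device is charged every other day.

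**3. Hourly versus window specificity.** The documents give no AUROC or hour-to-hour correlation, so these are assumptions: a normal index with equal variance 1 in both groups, 96 hours per window, and a constant within-window correlation (ICC) ρ.
- Separation: d = √2 × Φ⁻¹(AUROC). For 0.85, d = 1.466.
- Hourly specificity at 95% sensitivity: Φ(d − 1.645) = Φ(−0.179) = 0.43.
- SD of the window mean: s = √(ρ + (1 − ρ)/96).
- Specificity with 95% sensitivity set on the window mean: Φ(d/s − 1.645).

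| ρ | s | d/s | Window-mean specificity |
|---|---|---|---|
| 0.9 | 0.949 | 1.544 | 0.46 |
| 0.6 | 0.777 | 1.886 | 0.60 |
| 0.3 | 0.554 | 2.644 | 0.84 |

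The same formulas at other assumed values:

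| Hourly AUROC | Hourly specificity | Window mean, ρ = 0.9 to 0.3 |
|---|---|---|
| 0.75 | 0.24 | 0.26 to 0.53 |
| 0.85 | 0.43 | 0.46 to 0.84 |
| 0.90 | 0.57 | 0.60 to 0.95 |

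**4. The share of episodes missed can be below 5%.** Suppose a window counts as detected when most of its hours exceed the hourly cut-off. In simulation (AUROC 0.85, 96 hours, ρ from 0 to 0.9), 96% to 100% of ADHF windows are detected, and window specificity is 0.10 to 0.43. This majority rule is an illustration and is not in the article.

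**5. It can also be above 5%.** Take 48 episodes, k of them wholly missed with h usable hours each, and the rest fully detected with 96 hours each. Hourly sensitivity of 95% then requires k × h = 0.05 × [k × h + (48 − k) × 96], so k = 230.4 / (0.95h + 4.8).
- h = 96: k = 2.4 (5% of episodes).
- h = 24: k = 8.3 (17%).
- h = 12: k = 14.2 (30%).

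These are deliberate extremes. They show that an hourly 95% does not bound missed episodes when usable hours are uneven. An episode with no qualifying hour would not enter an hourly denominator at all.

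**The case against.** The strongest reply is that the article never says the ROC is run on hours. In Statistical analysis the hour is named only for the t-test. The ROC is there to assess the primary endpoint, which Table 4 words per episode. Labels start per visit, one exploratory objective counts regular episodes, and performance is examined up to 7 days either side of the diagnosis timestamp. On that reading, the aggregation rule is a detail that the full protocol or analysis plan may hold.

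Much of this stands. A reader might infer that the plan definitely fixes an hourly cut-off, but the documents do not state this. Nor do they support saying that 95% of hours is always the stricter demand, since step 5 shows the reverse is possible. The figures rest on assumed inputs, and at ρ = 0.9 the gap nearly closes (0.46 against 0.43).

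What remains is more than an omitted detail. The article does fix the hourly segmentation, filter, training unit and comparison unit, and then gives the operating point a per-event meaning that those steps do not deliver. An hourly ROC is the natural continuation of what is written.

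**Conclusion.** The point holds conditionally. The purpose of the 95% point and the primary endpoint are per event, the stated processing is per hour, and nothing shown connects them. If the ROC counts hours, the 95% does not fix the share of episodes missed, and the specificity beside it is not the event-level one. At an assumed hourly AUROC of 0.85 that means about 0.43 against 0.46 to 0.84 for ρ from 0.9 to 0.3. This is illustrative only, resting on a normal index and 96 complete hours per window.

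A reader might go further and infer that the study cannot support any conclusion on detecting episodes. The documents do not support that: the 95% point is an additional report, the primary AUROC is touched only through the same open unit, and the data allow an episode-level analysis. The matter should be settled before analysis.

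**What to change.** In Statistical analysis, state that the AUROC, the Youden cut-point and the specificity at about 95% sensitivity are computed with the annotated visit window as the unit. Each window gets one prespecified summary of its qualifying hourly index values, for example the mean. The mean is one option, and what matters is fixing the choice in advance. Keep hourly results as descriptive.

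At the chosen cut-off, report the number of ADHF windows missed and of regular windows flagged. Do not count alarms outside visit windows as false, because that time carries no clinical label.

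The cost is wording plus aggregation of values already computed, with no new data. The curve will have fewer points and a wider confidence interval.
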